#### Measures

##### Data from patient records

The following data will be collected from patient records at baseline and the 12-month time-point:Most recent clinical diagnosis as recorded in patient records using the Internal Classification of Diseases: 10th Revision classification.Most recent care cluster (a classification of mental health service users based on their needs, used in the NHS).Whether participants are subject to a care programme approach (NHS mental health services’ case management model).Service use during the previous 12 months measured at baseline and 12 months post study entry. Data will include history of use of acute mental health services, inpatient admissions and compulsory admissions and the number of kept and missed appointments with mental health services. Relapse of psychosis, the proposed primary outcome for a fully powered RCT, will be operationalised as participant admission to an acute mental health service (inpatient psychiatric wards, crisis houses, crisis resolution teams and acute day care services). This definition of relapse has been used previously in a recent trial of a self-management intervention in a mental health setting.^33^

##### My Journey 3 usage data

The data collected will be a record of each time the user opens My Journey 3, whether this was in response to a prompt, and which components they use. Usage data will not include participants’ text input or responses to self-rated questions, and will therefore not give any information regarding the mental health of users. Usage data will be solely used to assess the acceptability of My Journey 3 and user engagement with it.

##### Self-report questionnaires

The following are measured as potential secondary outcomes for a future fully-powered RCT:

Service use measures over 1 year of follow-up.Engagement with EIP services as measured by the Service Engagement Scale (SES),^34^ a 14-item questionnaire that measures engagement for four different dimensions: availability, collaboration, help-seeking and treatment adherence. The SES will be completed by EIP service clinicians, such as participants’ care co-ordinators, at baseline and at the 12-month time-point.

Measures at baseline, 4-month and 12-month follow-up assessments.Psychotic symptoms and general psychopathology, measured by the Positive and Negative Syndrome Scale (PANSS), a 30-item scale that yields three separate scores on positive symptoms, negative symptoms and general psychopathology.^35^ To inform the PANSS a trained researcher will conduct clinical interviews with participants at each assessment.Social outcomes, rated by the Social Outcomes Index (SIX),^36^ a 6-item index of social outcomes and circumstance.Mental health-related self-efficacy, measured by the Mental Health Confidence Scale,^37^ a 16-item self-report scale of service users’ confidence in their ability to cope with stressful or difficult events.Self-rated recovery measured by the Questionnaire about the Process of Recovery (QPR),^38^ a 22-item measure, yielding a total score and subscale scores for intrapersonal and interpersonal recovery factors.Mental well-being, rated by total score on The Warwick-Edinburgh Mental Well-Being Scale (WEMWBS),^39^ a 14-item self-report scale of mental well-being.Subjective quality of life and satisfaction with treatment measured by The DIALOG scale,^40^ an 11-item self-report scale.Socio-demographic characteristics including age, gender and ethnicity. We will also collect data regarding accommodation and living situation, employment status, educational attainment and Smartphone use, including use of other mental health apps.

##### Qualitative interviews

Interviews with participants in the intervention group will follow a topic guide and will explore their experience of using My Journey 3, including:The usability and acceptability of My Journey 3.Positives and negative aspects of My Journey 3.Impact of My Journey 3 on their life.Facilitators and barriers to using My Journey 3.Views on the training session.Views on the support they received from their clinician in using My Journey 3.

EIP service clinicians who have been supporting participants with My Journey 3 will also be asked to complete an audio-recorded interview close to the time the participant completes the 4-month follow-up assessment. Written consent to take part will be confirmed beforehand, with an information sheet provided. Clinicians will be asked to provide demographic data prior to undertaking the interview. The interview will follow a topic guide and will focus on:Positives and negative aspects of My Journey 3.The experience of supporting clients with My Journey 3.Facilitators and barriers to providing support and to the incorporation of My Journey 3 in clinical management.Views on the training session.

### Data analysis

No pre-specified criteria have been set for establishing the acceptability of My Journey 3 or the feasibility of trial procedures. The acceptability of My Journey 3 for EIP service users and clinicians will be determined from feedback given from the qualitative interviews and the level of participants’ My Journey 3 use indicated from the app usage data. Trial feasibility will be assessed from reviewing recruitment rates, drop-out rates and intervention enrolment and use during the trial period. These will be reviewed by the study team and discussed with stakeholders at a final dissemination event to decide on future steps to take.

#### Quantitative analysis

We will report rates of recruitment and retention in the trial, and, for the intervention group, the level of usage of My Journey 3 during the trial. The demographic and clinical characteristics of participants at baseline will be summarised separately for each study group using descriptive statistics.

To pilot the methods of analysis for a full-scale trial we will use an intention-to-treat approach using data from all randomised participants. The effect of My Journey 3 on relapse (the proposed primary outcome for a fully-powered RCT) during the 12-month trial period will be estimated using logistic regression. The effect of the intervention on continuous outcome measures (SIX, QPR, WEMWBS, DIALOG scale, PANSS and SES) will be estimated using linear regression adjusting for the baseline measure of the outcome in question. Results will be summarised using effect estimates and 95% CIs only. No interim analyses are planned.

#### Qualitative analysis

To assess the acceptability of My Journey 3 interview data with participants in the intervention group and supporting EIP service clinicians will be analysed based on The Theoretical Framework of Acceptability for healthcare system interventions.^41^ Analyses will be conducted collaboratively by a group of researchers.

### Patient and public involvement

Independent advice will be sought from a trial steering group. Members will include researchers with expertise in developing and testing digital health interventions, EIP service clinicians, people with lived experience of first-episode psychosis and carers. Steering group members with lived experience of psychosis were consulted on the first paper prototypes of My Journey 3 and on the research protocol. The version of My Journey 3 tested in the current feasibility trial has been developed based on EIP service users’ feedback from the usability tests and field study. Participants will be offered a summary of the research findings at the end of the study.

### Data monitoring and management

A secure password-protected trial database will be developed and managed to store all quantitative data using SPSS software V.23, and will feature non-identifiable trial IDs only. Data entry of participants’ questionnaires will be primarily undertaken by the trial researcher, with a random sample checked by other research team members. Anonymised electronic interview transcripts will be checked for accuracy and stored using NVivo for Windows (QSR International Pty Ltd V.11, 2016). After the trial, all data will be archived securely at University College London.

Due to the small sample size of the study a data monitoring committee is not planned, but the steering group will advise if one is later needed.

## Ethics and dissemination

### Confidentiality

Participant data will be accessed by the research team only. Consent forms and data collection forms will be securely stored in locked cabinets at University College London. Data collection forms will not feature participants’ names but a unique trial ID that could not be linked to participants by anyone outside the research team. Consent forms that identify participants will be kept separately from data collection forms.

Password-protected electronic data will be stored on the secure IT network at University College London. App usage data collected while using My Journey 3 will be anonymised and encrypted and will not contain personal user information.

### Serious adverse events

Serious adverse events such as hospital admissions and death reported to the trial team will be reviewed by the chief investigator. Identified adverse events assessed as trial-related will be reported to the trial sponsor.

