#### Delivery of the intervention

Each participant in the intervention group will take part in an individual training session with their supporting EIP service clinician and a researcher within 6 weeks of the initial consent meeting. During each training session participants will download My Journey 3 on to their Smartphone. The researcher will then give a demonstration of the app and its main functions. Participants will have the opportunity to practice using My Journey 3 and to ask questions. To facilitate use during the trial participants will be asked to input appropriate information in to the main functions of My Journey 3.

Participants will have access to My Journey 3 from the training session till the 12-month time-point. Participants in the intervention group will be free to withdraw from using My Journey 3, or decline the installation of it on to their Smartphone, without any impact on their study participation or their clinical care.

In line with evidence that clinician involvement increases user engagement with Smartphone apps,^32^ participants’ main contact for help with using My Journey 3 and the various intervention components will be their supporting EIP service clinician. Supporting EIP service clinicians will be encouraged by the researcher to discuss recovery goals and relapse prevention plans with study participants in routine appointments and then to assist participants in inputting them into My Journey 3. Clinicians will also be encouraged to regularly check with participants if they have been using My Journey 3 and if they need any further support with it. Clinician support will not be manualised. If supporting clinicians leave the participants’ EIP service the researcher will arrange a meeting to introduce any new clinicians that have clients using My Journey 3, to the intervention and how they can support service users that have access to the app. Researcher support with My Journey 3 will be limited to the initial installation and technical support as needed during the trial period.

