The research team will have no responsibility for providing clinical care if any My Journey 3 data shared by a participant to a third party indicates a decline in their mental health. If any major concerns regarding participants’ well-being such as suicidality arise from My Journey 3 data shared by a participant to the researcher, this would be communicated to the EIP service or other appropriate mental health services. Third parties such as EIP service clinicians and carers will not be briefed by the research team on how to respond to such information but would be expected to act as appropriate in such event. Participants will be informed at the training session that any data that may suggest a decline in their mental state that they have shared with EIP service clinicians or carers may be acted on accordingly, but that My Journey 3 is not suitable for seeking urgent medical care while in crisis.

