### Data collection

The participant timeline is summarised in table 1. All participants will be asked to complete self-report questionnaires during a structured assessment with a researcher at three time points: baseline (prior to randomisation), 4 months post baseline and 12 months post baseline. Participants in the intervention group will also be invited to complete an audio-recorded interview with a researcher during the 4-month follow-up assessments. Before arranging each assessment, the researcher will check with any clinicians in contact with the service users that the participant does not pose a risk to others and himself/herself and that it would be safe to conduct a research meeting. If there is an identified risk too serious for a meeting on NHS premises the participant will not be met for the assessment at that time-point, with the reason for not arranging a meeting documented. If any major concerns regarding participants’ risk or well-being arise during interactions with the researcher, this would be communicated to the appropriate EIP service.

**Table 1 T1:** Timeline of participant enrolment, interventions, assessments and patient records data collection

Time point	Enrolment	Baseline	Allocation	MJ3 training session*	4-month follow-up	12-month follow-up
Enrolment						
Eligibility screen	X					
Informed consent		X				
Randomisation			X			
Intervention						
My Journey 3 (intervention group)						
TAU (all participants)						
Assessments						
PANSS		X			X	X
Socio-demographic information		X			X	X
Clinical service use		X			X	X
Social Outcomes Index		X			X	X
Mental Health Confidence Scale		X			X	X
The Process of Recovery Questionnaire		X			X	X
WEMWBS		X			X	X
The DIALOG Scale		X			X	X
Service Engagement Scale (completed by EIP service clinicians)		X				X
Qualitative interviews (with participants in the intervention group and supporting clinicians)					X	
Patient records data (from previous 12 months to time point)						
Number of admissions to acute mental health services		X				X
Number of compulsory admissions to acute mental health services		X				X
Total number of days in acute care		X				X
Number of kept appointments with community mental health services		X				X
Number of missed appointments with community mental health services		X				X
Primary ICD-10 diagnosis		X				X
Most recent care cluster		X				X
Care Programme Approach status		X				X

*Participants in the intervention group only.

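### SAE review rests on events reported to an unblinded team with some app-arm-only contact routes, and is not linked to the admissions already drawn from patient records, so SAE counts could be incomplete and, if shown by arm, unequal

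*Protocol article*

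**What the plan says.** The protocol article gives serious adverse events two sentences. The first sets the route: "Serious adverse events such as hospital admissions and death reported to the trial team will be reviewed by the chief investigator". The second sets the onward step: "Identified adverse events assessed as trial-related will be reported to the trial sponsor". Neither mentions a search of records or a standard enquiry.

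Under Delivery of the intervention, the app arm has trial contact that the control arm lacks. "Each participant in the intervention group will take part in an individual training session with their supporting EIP service clinician and a researcher". After that, "Researcher support with My Journey 3 will be limited to the initial installation and technical support as needed during the trial period". If a supporting clinician leaves, the researcher arranges a meeting with the replacement. The same section provides that, if major concerns about well-being arise from "My Journey 3 data shared by a participant to the researcher, this would be communicated to the EIP service" or another appropriate service. Under Data collection, "Participants in the intervention group will also be invited to complete an audio-recorded interview with a researcher during the 4-month follow-up assessments". Under Qualitative interviews, "EIP service clinicians who have been supporting participants with My Journey 3 will also be asked to complete an audio-recorded interview".

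The Randomisation section says that allocation is not concealed from the research team once baseline is complete. Data monitoring and management plans no data monitoring committee.

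Admissions are also obtained by a second route. Data from patient records lists an extraction at baseline and at 12 months, not limited to one arm: "Data will include history of use of acute mental health services, inpatient admissions and compulsory admissions". That extraction supplies relapse, the proposed primary outcome of a full trial.

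**The concern.** Hospital admission is named as an SAE and is also part of the relapse definition. The protocol therefore captures admissions by two routes and does not say that they will be compared. The SAE route depends on someone telling the team. The team is open to allocation, and some of the occasions on which it might be told arise only in the app arm.

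Two things could follow. Admissions that nobody reports would be missing from the SAE log even though the trial holds them in its extracted data. And if SAEs are later tabulated by arm, a difference in reporting could pass for a difference in safety, or hide one. The protocol's aims include testing procedures for a definitive trial, so a weak SAE route would carry forward to it.

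**Working it through.** **The plan's own figure.** The Participants section asks for 12 completers per group at 40% attrition: 12 / (1 − 0.40) = 20 per arm, 40 in total. This reproduces. The point does not depend on it, except that any reconciliation covers 40 records.

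**Contact routes, side by side.**

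| Route to the team | App arm | Control arm |
|---|---|---|
| Assessments at 4 and 12 months, with service-use questions (Table 1) | yes | yes |
| Clinician check before each assessment (Data collection) | yes | yes |
| Training session, within 6 weeks of consent | yes | no |
| Technical support on request | yes | no |
| Handover meeting if a clinician leaves | yes | no |
| App data shared with the researcher | possible | no |
| Participant interview, during the shared 4-month visit | yes | no |
| Interview with the supporting clinician, around 4 months | yes | no |

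The asymmetry is real but limited. The training is early, and the participant interview falls at a visit that both arms have. Between months 4 and 12 neither arm has scheduled researcher contact; in the app arm, technical support, data sharing and handover meetings remain open, but only if the need arises.

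**What unequal reporting would do.** Let p be the true 12-month risk of admission, equal in both arms, and s the chance that an admission reaches the team. The document gives neither, so both are assumptions. Expected participants with a recorded SAE per arm = 20 × p × s. With a = p × s(app) and c = p × s(control), the apparent odds ratio = [a/(1 − a)] / [c/(1 − c)].

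Example: p = 0.30, s = 0.90 v 0.60. Then a = 0.27 and c = 0.18, the expected counts are 5.4 v 3.6, and the odds ratio is (0.27/0.73) / (0.18/0.82) = 1.68.

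| p | s app v control | Expected app v control | Odds ratio |
|---|---|---|---|
| 0.10 | 0.90 v 0.75 | 1.8 v 1.5 | 1.22 |
| 0.10 | 0.90 v 0.60 | 1.8 v 1.2 | 1.55 |
| 0.30 | 0.90 v 0.75 | 5.4 v 4.5 | 1.27 |
| 0.30 | 0.90 v 0.60 | 5.4 v 3.6 | 1.68 |
| 0.30 | 0.90 v 0.45 | 5.4 v 2.7 | 2.37 |
| 0.40 | 0.90 v 0.45 | 7.2 v 3.6 | 2.56 |
| 0.30 | 0.90 v 0.90 | 5.4 v 5.4 | 1.00 |
| 0.30 | 0.70 v 0.70 | 4.2 v 4.2 | 1.00 |
| 0.30 | 1 v 1 (all admissions found) | 6.0 v 6.0 | 1.00 |

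Across these unequal cases the difference runs from 0.3 participants (1.8 − 1.5) to 3.6 (7.2 − 3.6). The direction is put in by the choice of s. Swapping 0.90 and 0.60 at p = 0.30 gives 1/1.68, about 0.59.

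**Undercounting without any imbalance.** At p = 0.30 there are 12 expected participants with an admission. If 70% are reported in both arms, 40 × 0.30 × (1 − 0.70) = 3.6 of them are missing from the log, although the odds ratio is 1.00.

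**The case against.** A reader might infer that the trial's SAE comparison is biased against the app. The document does not support that. The Quantitative analysis section lists no between-arm comparison of SAEs. The one planned comparison of admissions is relapse, which comes from records in both arms. The extra contact makes unequal reporting plausible but does not show it, and the reporting rates used above have no source in the document.

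The shared safeguards also count for something. In both arms the researcher checks with clinicians before each assessment, the reason is documented when risk prevents a meeting, and service use is asked at 4 and 12 months. A clinician check is a likely way for an admission or death to become known in either arm. It is worded as a check on risk and on safety to meet, however, not as an adverse-event enquiry, and participants judged too great a risk are not seen at that time point.

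A second tempting reading is that the records are a complete SAE count and the log a partial copy of it. They are not. The extraction lists neither deaths nor non-psychiatric admissions. Relapse includes crisis houses, crisis resolution teams and acute day care, which need not be hospital admissions. The two counts can differ by definition, and the 12-month extraction comes too late for prompt review.

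Finally, a journal article condenses the full protocol, which may describe SAE procedures in more detail, and the published text does not bar events found in records from being reviewed. That limits the point. What stands is that the route actually stated is passive and is not tied to a source that the trial already collects.

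**Conclusion.** The point holds as a cheap improvement. As stated, SAE capture could be incomplete and, if counts are shown by arm, unequal. Neither the direction nor the size of an imbalance can be computed from the document. The odds ratios of about 1.2 to 2.6 illustrate one assumed direction and an assumed range of reporting; equal reporting gives 1.00 and leaves only undercounting. The relapse analysis does not depend on the SAE log.

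**What to change.** In the Serious adverse events section, keep spontaneous reports as the basis for prompt review. Add that at 12 months the SAE log will be reconciled, for every randomised participant in both arms, against the psychiatric admissions in the patient-record extraction and the service-use answers already collected at 4 and 12 months. Add death status to the extraction request. State that any SAE count by arm will come from the reconciled list, with the source of each event shown, and that hospital admissions will be distinguished from the wider relapse definition.

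The cost is a few sentences, one added data item and a small amount of clerical work on 40 records that are being extracted anyway. One gap remains: non-psychiatric admissions would still depend on reporting.

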### Dissemination

Results will be disseminated through scientific publications, and to a wider audience via magazines and web publications.
